### Recruitment {15}

The inclusion criteria for the NightLife study are broad, with participation to the main RCT accessible to the majority of adults receiving maintenance in-centre haemodialysis. Initially, patients at participating dialysis units will be ‘pre-screened’ to identify adults receiving maintenance haemodialysis (≥ 3 months of haemodialysis) who do not have a planned living-related kidney transplantation through liaison with the clinical teams. As randomisation to the intervention arm relies on the availability of an INHD appointment time within usual NHS service deliver, once an INHD appointment becomes available, pre-screened patients will be approached during routine haemodialysis sessions and formerly screened to confirm eligibility and gauge interest in the NightLife study. Patients interested in the study will be provided with a patient information sheet and be given a minimal of 48 h (i.e. 2 days between routine haemodialysis sessions) before they are revisited for re-discussion. At this second visit, the NightLife study discussion will either result in informed consent, study participation declined or study discussions paused (e.g. participant may require more time to consider their decision, or they would like to delay joining the study to a point that is more convenient around lifestyle factors such as work). The stages of pre-screening, screening and recruitment will be conducted by members of the research team (clinicians and research nurses) with Good Clinical Practice training.

The availability of INHD appointment slots is key to the ability of the research team to approach, consent and randomise participants. Consequently, recruitment rates will vary across sites according to their INHD status: *established* sites will already have an INHD service available and access to the study will compete with existing routine clinical care; *naïve* sites will set up an INHD service through the study and so the majority of the appointment times for INHD will be utilised by NightLife study participants. This creates two recruitment trajectories: one to two recruits per month at *established* INHD sites as appointments become available; and an initial large recruitment of participants (9 to 15) at *naïve* INHD sites as participants are randomised to either fill the INHD appointment times or remain on their usual haemodialysis. With only three participating sites providing an established INHD service, recruitment to the NightLife study will occur in stepwise manner as sites join. The NightLife study opened to recruitment in October 2021 and will close to recruitment in March 2024.

Recruitment and retention to NightLife was anticipated to be potentially challenging due to concerns around healthcare professionals’ and potential participants’ perceptions of equipoise. In particular, patient and public contributors expressed concern that patients may be disappointed and experience resentful demoralisation if not allocated to receive INHD. Resentful demoralisation can negatively impact study continuation and bias the results; participants allocated to the control arm may be more likely to drop-out or crossover, be more attentive to adverse event reporting and express lower quality of life [38–40]. This underscored the importance of conveying the rationale for NightLife and the potential benefits and disadvantages of the two treatment arms when presenting the RCT to potential participants [41]. An integrated QRI was incorporated into the NightLife protocol to understand and address factors that undermine recruitment and retention to the RCT. It comprises:Pre-emptive strategies to support recruitment, delivered prior to sites opening (e.g. training to raise awareness of clinical equipoise; strategies for explaining NightLife to potential participants with a view to safeguarding informed consent; input with preparation of patient-facing trial documentation, and designing tools to monitor recruitment, e.g. screening logs).Mixed methods to investigate recruitment and retention issues as they arise in NightLife, including (i) quantitative analyses of screening log data; (ii) semi-structured interviews with site personnel; (iii) audio-recordings of site personnel presenting the NightLife study to potential participants; and (iv) interviews with patients who accept and decline participation in the RCT. Data will be triangulated to crystallise key explanations for recruitment/retention issues [42].Delivery of tailored actions to address recruitment and retention issues as the RCT is underway, informed by findings from the above (‘b’) and discussion with the Trial Management Group.

Investigation of recruitment issues and delivery of tailored actions will proceed cyclically throughout the NightLife recruitment period.

### Assignment of interventions: allocation

#### Sequence generation {16a}

Participants will be randomised after informed consent has been provided and baseline questionnaire data collected. Allocation will be weighted towards to the intervention (1:1.33, control:intervention) to account for the assumed 25% conversion back to in-centre daytime haemodialysis from the intervention group within the first 2 weeks (see above). Randomisation will be stratified by haemodialysis unit and age (< 65 years, ≥ 65 years) and managed by the Leicester Clinical Trials Unit.

#### Concealment mechanism {16b}

Randomisation will be completed via a web-based system (Sealed Envelope) [43] to maintain allocation concealment.

#### Implementation {16c}

Randomisation is completed by the research team using a web-based system (Sealed Envelope) [43] once informed consent has been achieved and baseline questionnaire data have been collected.

### Assignment of interventions: blinding

#### Who will be blinded? {17a}

All analysis will be conducted by an assessor blinded to any patient data or intervention allocation; participants and investigators are not blinded due to the nature of the intervention and control.

#### Procedure for unblinding if needed {17b}

There is no requirement for a procedure to undertake unblinding as it is an open-label study.

### Data collection and management

#### Plans for assessment and collection of outcomes {18a}

Quality of life questionnaire data collection will be conducted by the research delivery teams at participating sites during haemodialysis appointments or over the telephone, at the convenience of the participant, to avoid additional study visits. Clinical information and results will be collected from routine clinical testing and medical records. Data entry will be completed by the researchers at participating sites. The NightLife study dataset will be analysed by the Leicester Clinical Trials Unit.

#### Plans to promote participant retention and complete follow-up {18b}

Study participation on the allocated treatment arm is 6 months. The baseline visit and all follow-up appointments are completed during usual routine haemodialysis appointments. There is the option for quality of life questionnaire data to be completed over the phone if more convenient to the participant. After baseline, the follow-up visits occur at 1, 3 and 6 months. Irrespective of KRT modality after study participation, capture of routine clinical data will take place on the 3-year anniversary of the last participant last visit.

For participants that leave their allocated treatment intervention (i.e. permanent crossovers), permission will be sought to continue to collect follow-up data. Some data may not be available due to death, kidney transplantation and voluntary withdrawal (these losses have been taken into consideration for the sample size calculation) or lack of completion of individual data items. Where possible, the reasons for missing data will be ascertained and reported. Although every effort will be made to minimise crossovers from both treatment arms, the numbers, direction and reasons for participants moving between arms will be recorded and reported in line with CONSORT (Consolidated Standards of Reporting Trials) guidance.

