### Additional consent provisions for collection and use of participant data and biological specimens {26b}

Informed consent includes access to medical records and linkage of research data to routine health data relevant to study follow-up. This trial does not involve collecting biological specimens for storage. Separate informed consent is required for the main RCT, embedded process evaluation and integrated QRI. Participation to the main RCT is not required for an individual to join the process evaluation or QRI.

There is an optional cardiac magnetic resonance imaging sub-study for participants joining the main RCT, for which additional informed consent is required. This sub-study protocol will be published separately and is not detailed in this manuscript.

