### Criteria for discontinuing or modifying allocated interventions {11b}

Participants may withdraw from complying with the allocated study treatment arm and/or providing data to the study, at any time, for any reason without affecting their usual care. Should a participant wish to withdraw from receiving their allocated study treatment, efforts will be made to continue to obtain follow-up data, with their permission. Participants do not have to give a reason for withdrawal; however, if they do provide a reason for leaving the study, this will be recorded.

The clinical team and/or investigators may discontinue a participant from the study at any time if considered necessary, e.g. based on symptoms and blood test results.

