## Statistical methods

### Statistical methods for primary and secondary outcomes {20a}

#### Primary outcomes

The primary outcome will compare the KDQoL composite score over 6 months between the intervention and control. The primary outcome analysis will be conducted using a modified intention to treat with participants with at least one post baseline measurement of KDQoL analysed in the groups to which they were randomly allocated, regardless of haemodialysis schedule they actually received. The KDQoL total score over 6 months (i.e. 1, 3 and 6 months) will be compared between the treatment arms using a repeated measures mixed linear regression model with participant as a random effect to account for repeated measures over time. The model will be adjusted for a treatment group, minimisation factors (haemodialysis unit and age) with haemodialysis unit as a random effect and baseline KDQoL total score. Treatment comparison estimates will be presented as adjusted mean difference and 95% confidence intervals.

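### Follow-up after leaving the allocated schedule depends on permission sought at that moment; refusals would fall mainly in the INHD arm and shift the primary estimate toward adherers

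*Protocol article*

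**What the plan says.** Two sections of the protocol article govern data collection once a participant leaves the allocated schedule. Plans to promote participant retention {18b} states: "For participants that leave their allocated treatment intervention (i.e. permanent crossovers), permission will be sought to continue to collect follow-up data". Criteria for discontinuing or modifying allocated interventions {11b} says that, after a participant stops the allocated treatment, "efforts will be made to continue to obtain follow-up data, with their permission". The same paragraph of {11b} lets a participant give up the treatment arm, the provision of data, or both, so it regards these as two decisions. On the scope of consent at entry, section {26b} says: "Informed consent includes access to medical records and linkage of research data to routine health data relevant to study follow-up".

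Three further statements fix the timing and the analysis set. Sequence generation {16a} weights the allocation because of an "assumed 25% conversion back to in-centre daytime haemodialysis from the intervention group within the first 2 weeks". Section {18b} gives the visit schedule: "After baseline, the follow-up visits occur at 1, 3 and 6 months". The primary analysis is a "modified intention to treat with participants with at least one post baseline measurement of KDQoL analysed in the groups" to which they were randomised, whatever schedule they received.

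Section {20c} prescribes a complete case analysis when KDQoL is missing for under 5% of participants and multiple imputation at 5% or more. Crossover is not expected in one arm alone. Section {18b} says "Although every effort will be made to minimise crossovers from both treatment arms", and Recruitment {15} warns that "participants allocated to the control arm may be more likely to drop-out or crossover".

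**The concern.** A change of dialysis schedule is not a withdrawal from the study, yet it is the event that prompts a request for permission to go on collecting data. As worded, the request covers all follow-up. That includes routine dialysis-unit data, which need nothing more from the participant and which the consent at entry appears to cover through records access and linkage.

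In many trials this would be a small matter. Here the plan itself predicts that a quarter of one arm will reach this point, and will do so before any outcome has been measured. A reverter who declines has no post-baseline KDQoL and so fails the entry condition of the primary analysis set. The reason for the loss is bound up with how the participant fared on INHD. Removing such people moves the comparison away from the effect of offering INHD and toward the effect in those who stay on it.

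The same people are needed for the planned complier average causal effect analysis and for the assessment of how switching affects the treatment effect, both in section {20b}. Those who refuse could also be lost to the adherence and SAE summaries.

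**Working it through.** **Inputs from the protocol article.** Allocation is 150 control and 200 INHD. The standardised difference is 0.26, the correlation with baseline 0.78, power 90%, type I error 5% and evaluable number 252. Overall attrition is 15% and INHD non-adherence 25% (all Sample size {14}). Reversion is expected within 2 weeks ({16a}) and the first follow-up KDQoL is at 1 month ({18b}).

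**Inputs assumed.** The test is two-sided. The refusal fraction *f* among reverters is not documented, so a range is shown. The effect is 0.26 SD in adherers and zero in reverters; the plan states 0.26 as the difference between groups, so this split is a model. There are no control refusals, no other loss and no imputation, and reverters do not otherwise differ in prognosis.

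**1. The plan's own figures.** The SD after baseline adjustment is √(1 − 0.78²) = 0.626. With a difference of 0.26, two-sided 5% and 90% power, the total is 244 at 1:1 and 250 at 1:1.33, against 252 stated. Inflating 126 per arm gives 126/0.85 = 148.2 for control and 126/0.85/0.75 = 197.6 for INHD. The total is about 346, against 350 stated. The figures reproduce closely. The plan counts attrition and non-adherence separately, so reverters are budgeted as non-adherent, not as lost.

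**2. Number reaching the request early.** 0.25 × 200 = 50 INHD participants, before the first follow-up score.

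**3. Effect with full follow-up.** (150/200) × 0.26 = 0.195 SD.

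**4. Effect when a fraction *f* of the 50 refuse.** The retained INHD arm is 200 − 50*f*, so the estimate is 150/(200 − 50*f*) × 0.26.

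| *f* | INHD lost | Share of 350 | Estimate (SD) | Change from 0.195 |
|---|---|---|---|---|
| 10% | 5 | 1.4% | 0.200 | +3% |
| 25% | 12.5 | 3.6% | 0.208 | +7% |
| 50% | 25 | 7.1% | 0.223 | +14% |
| 100% | 50 | 14.3% | 0.260 | +33% |

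The last row is the limit in which only adherers remain. It would use nearly all of the 15% attrition allowance in one arm.

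**5. The imputation threshold.** 5% of 350 is 17.5, and 17.5/50 = 35%. Below 35% refusal, these losses alone would not trigger imputation.

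**6. Crossover in the control arm.** No rate is given. At an assumed 5% or 10% of 150 (7.5 or 15 people) and equal refusal rates, the INHD share of refusals is 50/57.5 = 87% or 50/65 = 77%.

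**7. Prognosis of reverters.** If reverters also score lower for other reasons, losing them adds to the shift; if they score higher, it subtracts. Take an assumed deficit of 0.3 SD and 40% refusal. The reverter share of the arm falls from 50/200 to 30/180, a drop of 0.083. A deficit that arises wholly after baseline adds 0.083 × 0.3 = 0.025 SD. If it is already present at baseline, adjustment leaves 0.3 × (1 − 0.78) = 0.066 SD, which adds only about 0.0055 SD.

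**The case against.** The case on the other side has real weight.

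- **Both arms can cross over.** A reader might infer that every refusal falls in the INHD arm. Sections {15} and {18b} rule that out by foreseeing control crossovers. What stands is that the only quantified, early switching is in the INHD arm.
- **The result need not become a per-protocol one.** A reader might also infer that the analysis would rest on adherers alone. That needs every reverter to refuse, and nothing in the document suggests it.
- **The text aims at retention.** Section {11b} promises efforts to keep collecting data, and no passage says that collection stops unless permission arrives. That is fair, but those efforts remain conditional on permission, and the text does not say what happens in its absence.
- **Imputation is planned.** At 35% refusal or more it would be triggered by these losses alone. With 15% attrition assumed overall, other losses may well trigger it sooner. Even so, it is unclear whether imputation reaches people whom the primary analysis set excludes for having no post-baseline score. The more reverters decline, the fewer observed reverters there are to inform it.
- **The consent form is not shown.** Section {26b} names records and linkage; it does not say that questionnaires after a change of schedule are covered. The article condenses a fuller protocol, which may contain graded withdrawal options. This limits what can be said of participants already enrolled, but not the criticism of the rule as stated.
- **Reverters remain reachable.** They return to in-centre dialysis three times a week, and telephone completion is already available. Failure to ask in time is therefore an unlikely route of loss; refusal is the one that matters.
- **Participants may always decline.** That is right, and some refusals would occur under any wording. How many the change would prevent cannot be estimated from the document.

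**Conclusion.** The concern holds in a limited form. The stated rule ties continued data collection to permission at the moment of leaving the schedule, and the plan predicts that about 50 of 200 INHD participants will reach that moment before the first follow-up KDQoL. Refusals would remove people from the primary analysis set mainly in that arm and would shift the estimate toward adherers. Under the stated model the shift is +3% to +14% of the full-follow-up effect for refusal between 10% and 50%. Its size, and in principle its direction, also depend on how reverters fare.

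The document does not support saying that the loss is confined to one arm, that the result is reduced to adherers, or that SAE and adherence data are lost for reverters in general; this last applies only to those who refuse. The sample-size allowance for losses protects power but does not remove bias from unequal loss. The point merits a change because the remedy is cheap and the triggering event is one that the plan expects. Confidence is medium, since the refusal rate is unknown.

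**What to change.** In sections {11b} and {18b}, state that a change of schedule in either arm, temporary or permanent, is not a withdrawal from the study. Questionnaires (with the existing telephone option), routine dialysis data, SAEs and linkage then continue as scheduled under the consent given at entry, unless the participant asks to stop. When a participant does ask, record separately which elements stop: questionnaires, routine data or linkage. For participants already enrolled, apply this as far as their signed consent allows.

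The cost is an amendment to the protocol wording, a graded withdrawal form and a matching line in the information sheet for new participants. No visits are added, and the right to withdraw from data collection is unchanged.

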### Data management {19}

A validated web-based Remote Data Capture system provided by the Leicester Clinical Trials Unit will be used for data entry. The NightLife study dataset will be held by the Leicester Clinical Trials Unit. Source data will also be documented on case report forms and stored securely at participating centres in study investigator site files.

### Confidentiality {27}

All participants will be allocated an individual trial identification number. Participants’ personal data included in study-related databases shall be treated in confidence and in compliance with ICH-GCP, the UK Policy Framework for Health and Social Care, and the EU General Data Protection Regulation (GDPR). When processing or archiving personal data, the Sponsor or its representative will take all appropriate measures to safeguard and prevent access to this data by any unauthorised third party.

### Plans for collection, laboratory evaluation and storage of biological specimens for genetic or molecular analysis in this trial/future use {33}

Biological specimens are not being collected for the NightLife study. Blood and urine results for the secondary outcomes are obtained from routine clinical testing, and are all handled in UK NHS laboratories.

## Statistical methods

### Statistical methods for primary and secondary outcomes {20a}

#### Primary outcomes

The primary outcome will compare the KDQoL composite score over 6 months between the intervention and control. The primary outcome analysis will be conducted using a modified intention to treat with participants with at least one post baseline measurement of KDQoL analysed in the groups to which they were randomly allocated, regardless of haemodialysis schedule they actually received. The KDQoL total score over 6 months (i.e. 1, 3 and 6 months) will be compared between the treatment arms using a repeated measures mixed linear regression model with participant as a random effect to account for repeated measures over time. The model will be adjusted for a treatment group, minimisation factors (haemodialysis unit and age) with haemodialysis unit as a random effect and baseline KDQoL total score. Treatment comparison estimates will be presented as adjusted mean difference and 95% confidence intervals.

#### Secondary outcomes

The secondary outcomes will be analysed using linear regression for single point in time continuous outcome measures; repeated measures mixed linear regression model for secondary outcomes measured repeatedly over time; and logistic regression for binary measures. All analyses will be adjusted for baseline value and the minimisation factors (haemodialysis unit and age). The number of deaths and cardiovascular events expected is relatively low; therefore, formal time to event analyses will not be conducted. Kaplan–Meier will be presented to describe the relationship between these events and treatment.

### Interim analyses {21b}

No interim analyses have been pre-defined; formal interim analyses where the treatment groups are compared to evaluate primary or secondary outcome measures are not planned.

### Methods for additional analyses (e.g. subgroup analyses) {20b}

There is increasing demand by clinicians and patients for ‘per-protocol’ analyses which quantify the effect of being randomised to, receiving and continuing a treatment [44]. A secondary, complier average causal effect (CACE) analysis will be conducted to understand the efficacy of extended-hours INHD in those that receive it as planned.

Clinical experience suggests that the development of new conditions which cause instability of the patient whilst they are on haemodialysis may mean that patients allocated to INHD will have to return to usual care during the day. The effect of such switching on the treatment effect found will be assessed.

Subgroup analyses will be limited to the same variables used as minimisation variables. Tests for statistical heterogeneity (e.g. by including treatment group by subgroup interaction parameter in the regression model) will be performed prior to any examination of effect estimate within subgroups.

